### Adverse events and safety evaluation

All adverse events (AEs) will be documented in the patient file and Case Record Form (CRF) by a trained project research scientist daily during intervention procedures and over phone or on every visit after that. Any associated diseases, conditions or symptoms that present at screening and will persist throughout the intervention without any change will not be considered as an adverse event and will be documented at the time of screening. Laboratory investigations as a part of safety evaluations will involve routine blood and urine investigations prior to initiation and upon completion of the treatment protocol or as and when required along with periodic clinical monitoring of vital signs and general physical health. Participants will be asked to report any new AE/symptoms at any time during the trial. Any reported or observed AE as per CTCAE v5.0 ≤ Grade 2 will be managed by the supportive care and intervention will be continued if it is not persisting after that. Expected AEs and its management are detailed in Table 3. All reported AE ≥ 3 will be reported to principal investigator and the ethics committee.

**Table 3 tab3:** Expected adverse events and management.

Procedure/intervention	Expected adverse events	Management plan
Snehapāna(internal oleation)	General weakness, nausea, diarrhoea, abdominal pain, headache, belching and bloating, intolerance to snehapāna	Administering dried ginger water and Aṣṭacūrṇa as a rescue medicine for enhancing the digestion of sneha, adjusting the subsequent dose of snehapāna
Vamana (therapeutic emesis)	General weakness, diarrhoea, dehydration, hypotension, dizziness, mild abdominal discomfort, and loss of appetite	Hydration, diet plan, which is easily digestible, rest
Virecana (therapeutic purgation)	Mild abdominal cramping, dizziness, hypotension, excessive purgation, nausea and vomiting	Adequate hydration with warm water, buttermilk and rice water as rescue measures
Yoga basti (course of eight combined therapeutic enemas)	Abdominal cramping, rectal irritation, incomplete evacuation	Sthānika abhyanga and swedana (massage with oil over abdomen and pelvis) and oral hydration
Uttara basti (administration of therapeutic oil or ghee via vagina)	Mild pelvic discomfort, abdominal cramps, bloating, mild injury and spotting from cervix, hypotension, pelvic infection	Abhyaṅgaḥ and svedana (application of oil and sudation over lower abdomen), oral hydration, Yaṣṭimadhu taila yoni pichu (vaginal tampoon soaked with Yaṣṭimadhu taila inserted in the vagina) as a rescue measure for cervical injury, yoniprakṣālana (medicated vaginal douche) in case of infection
Oral medications	Mild abdominal discomfort, nausea, diarrhoea, anorexia	Water boiled with dried ginger water, temporary dose modification and diet plan which is easily digestible

The intervention will be discontinued if:

The participant experiences any Grade ≥3 AERepeated Grade 2 AEs persist despite appropriate management.The participant withdraws consent at any stage.Occurrence of pregnancy.

Participant safety will be monitored continuously by the principal investigator and the study team. Oversight will be provided by the Institutional Ethics Committee, which retains the authority to recommend continuation, modification, or termination of the study if significant safety concerns arise. The invasive procedures like Uttara basti and Yoga basti will be done only under the governance of project research scientist who holds a post graduate degree and received proper training. All aseptic precautions will be taken prior to the procedure. Participants will be confirmed of immunized to Tetanus before invasive procedures like Uttara basti. Any AEs reported during or after the procedure will be reported carefully and will be informed to the principal investigator and appropriate measure will be taken immediately. To prevent any potential possibilities of harming the mother and foetus, in case of an unintended pregnancy, all the participants will be given proper counselling to refrain from sexual intercourse throughout the study duration. All the medicines used for the clinical trial will be procured from Amrita Life, a GMP-certified company. To guarantee the authenticity, safety and uniformity, all the batch of trial medications will undergo predefined QC analysis of the manufacturer. The batches meeting all the standards, with a certificate of analysis, will only be used for the clinical trial.

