## Introduction

Infertility is a disorder that impacts an individual’s psychological and social aspects (1). The treatment of infertility is mainly focused on its cause. With the advancement in medical sciences, assisted reproductive technique (ART) can now overcome major issues causing infertility (2). But the successful outcome of all these treatment modalities is completely based on one’s ovarian reserve. Ovarian reserve depicts the quality and quantity of oocytes remaining in the ovaries (3). It thus gives an idea about ovarian function or reproductive age at a given time. Because of aging, ovarian reserve diminish physiologically. But many women face a non-physiologic reduction of ovarian reserve, irrespective of age. The non-physiological reduction may result from multiple factors like autoimmune diseases, environmental pollution, psychological factors, genetic factors, endometriosis, pelvic inflammatory disease and chemotherapy (3). It has been reported that DOR is one of the leading reasons for seeking ART, with approximately 26% of patients undergoing ART due to this condition (4). DOR may be associated with irregular menstruation, hypomenorrhea, amenorrhea, short follicular phase, and poor ovarian response (5). Clinical assessments of DOR are done through ultrasonography by counting the number of ovarian antral follicles (AFC), and serum anti-mullerian hormone (AMH) test (6). DOR patients are being managed through conventional medicine by different stimulation protocols, Hormone replacement therapy (HRT), and Dehydroepiandrosterone (DHEA) as pre-treatment to IVF. It was observed that even after ovarian hyperstimulation with high-dose gonadotrophin, DOR patients have a smaller number of oocytes, a low fertilization rate, and a higher cycle cancellation rate (7). Most patients are ultimately left with the only option of IVF with a donor egg (8). But proper evidence is lacking to support their role in DOR (9). Also, the mode of action of these medicines is still unknown (10). Hence, identifying effective treatment modalities for DOR becomes an area of great clinical relevance.

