## Methodology

### Ayurvedic interventions

Women diagnosed with DOR and satisfying the eligibility criteria will be recruited at Amrita Fertility Centre. After due consent, these participants will be subjected to Ayurvedic treatment protocol at Amrita School of Ayurveda.

The intervention protocol begins with śodhana karma (cleansing therapy) and śamana karma (medicines for restoring normalcy or pacifying action). The medicines and formulations selected in the protocol will be individualized according to the participant’s clinical status but follows a standardized therapeutic framework (Table 2).

**Table 2 tab2:** Treatment protocol.

Treatment protocol and interventions—Śodhana karma (cleansing therapy)		
Treatment procedure	Method of administration	Treatment duration
Dīpana, pācana (stimulating digestive fire or appetizing action) with Vaiśvānara cūrṇa (24)	5 g twice daily before food with warm water	Day 1–2
Snehapāna (internal oleation). with appropriate ghee or oil	Ārohaṇakrama (gradually increasing dose) after assessing the agni (digestive, metabolic factors) and koṣṭha (bowel habit)	Day 3–8
Sarvāṅga abhyaṅga and svedana (Oleation and sweating treatment)	Sarvāṅga abhyaṅga (application of oil on whole body) with Dhanvantara taila followed by nāḍīsveda (sweating induced by steam directed from hose)	Day 9–10 for vamana Day 9–day 11 for virecana
Either Vamana (therapeutic emesis) or virecana (therapeutic purgation) (25)	Avipatti choorna 30 g given at 7 a.m. for Virecana	Vamana on Day 10 and Virecana on Day 11
Yogabastiḥ (course of eight combined therapeutic enemas)	Three Nirūhabasti (therapeutic decoction enema) with 750 mL of Mustadiyapanabasti and five anuvasanabasti (therapeutic oil enema) with 150 mL of Mahānārayaṇataila administered on alternate days (26)	Day 13–20
Uttarabasti (administration of therapeutic oil or ghee via vagina)	With 3 mL Mahānārayaṇataila into the uterine cavity on the day of Nirūhabasti	
Śamana karma (medicines for restoring normalcy or pacifying action)		
Medicine	Dose	Time and route of administration
Kalyanaka Ghrita/Phala sarpi (medicated ghee) (27)	10 mL	Morning in empty stomach orally
Mahanarayana taila (medicated oil) (28)	10 mL	Evening in empty stomach orally
Satapushpa choorna/Hinguvachadi choorna (medicines in the form of powder) (29, 30)	5 g	Twice daily before food mixed with ghee in the morning and oil in the evening, orally

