Śodhana karma (cleansing therapy): the participant will be admitted for a maximum of 21 days following the cessation of menstrual bleeding in the first menstrual cycle. The trial intervention begins with dīpana (stimulating digestive fire or appetizing action) and pācana (digestive action) by administering Vaiśvānara Cūrṇa for 2 days. This is intended to enhance the digestive capacity of the participant and prepare them for the subsequent procedure, snehapāna (internal oleation). Snehapāna (internal oleation) is done by the oral administration of medicated ghee or oil in gradually increasing doses until signs of adequate oleation or samyak snigdha lakṣaṇas are observed or for up to a maximum duration of 7 days. The selection of medicine, dose and duration of snehapāna (internal oleation) will be decided based on the agniḥ (digestive, metabolic factors), koṣṭhaḥ (bowel habit) and clinical condition of the participant. Adequate oleation ensures that the body is properly lubricated for detoxification. Snehapāna (internal oleation) is followed by svedana (sudation therapy) which will be performed for 2–3 days which further facilitates the śodhana karma (cleansing therapy). These preparatory procedures together constitute the pūrvakarma (preparatory phase) of śodhana karma (cleansing therapy).

Depending on clinical indications, participants will then undergo vamana (therapeutic emesis) or virecana (therapeutic purgation), which constitute the main śodhana (cleansing) procedures.

In the concluding part of the śodhana karma (cleansing therapy), participants will receive basti karma (therapeutic enema), which involve medicated enemas. Two forms will be administered:

Yogabasti (course of eight combined therapeutic enemas)—a combination of five snehabastiḥ (therapeutic oil enema) and three nirūha basti (therapeutic decoction enema) given alternately over 8 days.Uttarabasti (administration of therapeutic oil or ghee via vagina)—will be performed on the same day as the nirūha Basti, aimed at directly nourishing and rejuvenating the reproductive organs and their functions.

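### Table 3 names only a vaginal douche for pelvic infection after intrauterine oil, and nothing bars re-instillation once an infection of Grade 2 or lower is judged settled

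*Protocol article*

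**What the plan says.** All references are to the protocol article.

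- **Route and schedule.** Table 2 (*Ayurvedic interventions*) gives uttarabasti as 3 mL of medicated oil "into the uterine cavity on the day of" the decoction enema. The text of that section describes five oil enemas and three of the other kind ("therapeutic decoction enema) given alternately over 8 days"), and says uttarabasti "will be performed on the same day as the" decoction enema.
- **Expected events.** The uttara basti row of Table 3 (*Adverse events and safety evaluation*) includes "mild injury and spotting from cervix, hypotension, pelvic infection".
- **Management.** The same row offers oil and sudation over the lower abdomen, oral hydration, a medicated vaginal tampon for cervical injury and, for infection, yoniprakṣālana ("medicated vaginal douche) in case of infection").
- **Continuing.** An event of CTCAE v5.0 Grade 2 or lower receives supportive care, and the "intervention will be continued if it is not persisting after that".
- **Stopping.** The list has four items: any event of Grade 3 or higher, repeated Grade 2 events that persist despite management, withdrawal of consent, and pregnancy.
- **General clause.** Events during or after the invasive procedures are reported to the principal investigator and "appropriate measure will be taken immediately".

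**The concern.** Oil is placed in the uterine cavity, and the event foreseen is infection of the pelvis. The one measure named for it acts in the vagina. Neither the douche nor the other measures in that row are treatment for infection of the uterus or pelvis. That is a clinical judgement and needs no figure from the document.

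The continuation rule then treats this infection like any other mild event. If it is graded 2 or lower and looks settled after supportive care, the course resumes, and the next step may be another intrauterine instillation into a recently infected and possibly undertreated tract.

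The participants already have low ovarian reserve and are heading for oocyte retrieval. The Introduction lists "endometriosis, pelvic inflammatory disease and chemotherapy" among the factors that may reduce ovarian reserve. Harm to the ovarian function that AMH and AFC are meant to reflect is therefore a plausible concern, though not a shown effect.

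**Working it through.** The plan gives no figure to reproduce here. The check is to read the rules together and count what remains of the course.

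**1. Is the route intrauterine?** The treatment name is glossed as administration via the vagina, but the administration column of Table 2 specifies the uterine cavity. The second is the operative instruction.

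**2. How many instillations, and how far apart?** One per decoction enema gives 3 per woman, and 3 × 3 mL = 9 mL. The enemas run from Day 13 to Day 20. Their order is not printed. If the three decoction days are two days apart, which is how I read alternate giving, four placements fit:

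| Decoction days | Gaps | First to last |
|---|---|---|
| 13, 15, 17 | 2, 2 | 4 days |
| 14, 16, 18 | 2, 2 | 4 days |
| 15, 17, 19 | 2, 2 | 4 days |
| 16, 18, 20 | 2, 2 | 4 days |

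The spacing is the same in every case.

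**3. What is still scheduled when an infection appears?**

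| Infection after | Instillations left | Volume left |
|---|---|---|
| first | 3 − 1 = 2 | 2 × 3 = 6 mL |
| second | 3 − 2 = 1 | 1 × 3 = 3 mL |
| third | 3 − 3 = 0 | 0 mL |

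**4. What do the rules do with the remainder?**

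| Infection | Continuation rule | Stop list | Result as printed |
|---|---|---|---|
| Grade 3 or higher | does not apply | met | intervention stops |
| Grade 2 or lower, judged not persisting | continue | not met | remaining instillations permitted |
| Single episode, Grade 2 or lower, persisting | no permission to continue | not clearly met, since the item needs repeated Grade 2 events | not clearly covered |
| Repeated Grade 2, persisting | no permission to continue | met | intervention stops |

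The second row is the defect. The third is a smaller gap that the same fix closes.

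**5. Does another provision fill the second row?** Asepsis, tetanus immunisation and a trained operator are preventive and do not govern what follows an infection. Safety laboratory tests are set before and after the treatment protocol and otherwise as needed, so none is fixed before a repeat instillation. The clause on appropriate measures sets no specific action.

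**The case against.** The strongest reply is that the protocol already puts clinicians in charge. Events are documented daily during the procedures by a research scientist who is a specialist doctor. Any event of an invasive procedure goes to the principal investigator, described under *Data collection* as a professor of reproductive medicine. Table 3 does not call the douche exclusive or forbid antibiotics, and staff also work to the centre's standard operating procedures, where a condensed article may leave such detail. This stands in part: the absence of the word antibiotics would be weak ground alone. But the article does print a specific measure for this infection, and it is the wrong kind. A general clause does not replace a specific instruction. Treatment is also given in Kollam, while the principal investigator is described at the fertility centre in Kochi, so on-site staff are likely to turn first to the written plan.

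A reader might infer that the rules let the course run on after any pelvic infection. They do not. Permission is limited to Grade 2 or lower and to events that are not persisting. With instillations two days apart, an infection must appear, be treated and settle inside that gap for the next one to go ahead on time. The document does not give the CTCAE grade of a typical pelvic infection. If most were Grade 3 or higher, the stop rule would usually apply and mainly the treatment wording would be at issue.

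A reader might also want the chance of an infection in the trial. The document gives no risk per instillation, so such a figure would only restate an assumption. Nor can re-instillation follow a woman's third instillation.

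**Conclusion.** The point holds within limits. Table 3 prints an inadequate measure for an infection that the protocol itself expects. The continuation rule and stop list, read together, permit up to two further intrauterine instillations (6 of 9 mL) after a first episode of Grade 2 or lower that is judged settled. This rests on three instillations per woman, a 2-day spacing inferred from the alternating schedule, and the clinical premise that a vaginal douche does not treat uterine or pelvic infection.

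How often this would arise is unknown. It would also go too far to infer that the trial's AMH or AFC results will be lowered: the Introduction names pelvic inflammatory disease only as a possible cause of reduced reserve and says nothing about a settled mild infection affecting either marker by Visit 3. The case for change is patient safety at almost no cost. It is a change to consider, not an objection to the design as a whole.

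**What to change.** In the uttarabasti row of Table 3, replace the douche for infection with:

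*Suspected pelvic infection of any grade: hold uttarabasti, prompt gynaecological assessment, and antibiotic treatment by the centre's standard if infection is confirmed or judged likely.*

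Add after the discontinuation list in *Adverse events and safety evaluation*:

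*No further uttarabasti is given once pelvic infection is confirmed or judged likely, whatever the grade; the rule for continuing after events of Grade 2 or lower does not apply to it. Omitted instillations are recorded, and the woman stays in follow-up to Visit 3.*

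Mild discomfort, cramps or bloating alone stay under the existing text. A permanent stop on mere suspicion would go further than needed, because those symptoms are themselves expected after the procedure. A hold pending assessment is enough.

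The cost is one table cell, one added passage and one CRF item for omitted instillations, with assessment and any antibiotics only for affected women. No extra participants or scheduled visits are needed. The downside is that an affected woman may miss up to two of her three instillations.

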### Multiomics analysis methodology

#### Transcriptomics of granulosa cells

Follicular fluid collected will be aspirated and pooled during the retrieval of oocytes. Granulosa cells will be isolated from the follicular fluid by centrifugation at 700 g for 10 min using percoll-mediated density gradient centrifugation. The layer with the cells will be carefully removed using a pipette and transferred to a fresh tube with the cell storage medium (10% FBS with DMSO). Total RNA will be extracted from the cells using TRIzol reagent. RNA purity and concentration will be assessed using Nanodrop2000 spectrophotometer (Thermo Fischer Scientific) with samples showing A260/280 between 2.0 to 1.8 considered acceptable and outsourced to MedGenome, Bangalore, India for library preparation and RNA sequencing. The quality of the raw reads will be checked using FastQC and MultiQC. Adapter trimming and low quality read removal will be performed using Trimmomatic v0.39 and the resulting clean reads will be aligned to the human reference genome with STAR (v2.7.10a). Gene counts will be obtained with feature Counts (v2.0.3) and analysed using DESeq21.34.0 in R software. Differential gene expression profiles will be analyzed comparing the control and treatment samples. False positives will be analyzed through Benjamini–Hochberg correction method. The adjusted *p*-value (FDR) less than 0.05 will be considered statistically significant. Following normalization, the gene enrichment analysis will be performed. The top upregulated and downregulated genes (≥1.5-fold) will be further validated using qRT-PCR using specific primers for the selected genes. The relative quantification of genes will be performed through comparative CT analysis.

#### Proteomics of follicular fluid

The follicular fluid collected will be subjected to percoll-mediated density gradient centrifugation. The samples will be centrifuged at 700 g for 10 min and the supernatant containing the follicular fluid proteins will be transferred to a fresh tube. Further, protein estimation will be performed using BCA assay. Since quantitative proteomics needs to be performed through in-solution trypsin digestion, the high abundant proteins present in the follicular fluid will be enriched using Proteominer enrichment kit from Bio Rad. The enriched protein fractions will be eluted, and further protein estimation was done using BCA assay. These protein samples will be resolved on a 15% SDS-PAGE gel to see the overall protein profile after protein enrichment.

100 μg of protein samples will be used for in-solution protein digestion. To achieve this, reduction will be performed using dithiothreitol (100 mM, incubated at 56 °C for 45 min) and alkylation using iodoacetamide (250 mM, incubate for 30 min at RT in the dark). The resulting solutions will be digested using trypsin (1:20 ratio), followed by incubation at 37 °C overnight. The digestion process will be terminated after 16 h by adding 0.1% FA. The solution containing the digested peptides will be subjected to TMT labelling (10 plex) for protein quantification (31). The TMT labelled peptide samples will be desalted and subjected to mass spectrometry analysis. The peptides will be resolved through a C-18 reversed phase column (Agilent ZORBAX SB-C18, 75 μm × 150 mm, 5 μm) having a 40 nL enrichment column also. The samples will be infused to the mass spectrometer through a capillary/nano HPLC equipped with a chip cube source. The mass spectrometric data will be collected in positive ionization mode. The mobile phase solvents will be; A-water+ 0.1% formic acid; B-acetonitrile: water in 90:10 ratio. The enzymatic digests will be resolved across the column using a linear gradient of 5–45 %B in 30 min; 45–90 %B in 20 min. The other parameters that will be used for the data acquisition are: MS; 250–3,000 m/z, MS/MS; 50–3,000, collision gas-nitrogen, capillary voltage; 2000 V, dry gas; 5 L/min, fragmentor voltage; 150 V, source temp; 350 °C, MS and MS/MS scan speed; 4 & 3 spectra/s, respectively. Number of precursors; 5, preferred charge states; trypsin (2, 3, >3). The data will be acquired using MassHunter (Version 6.0) software from Agilent Technologies. The raw data obtained after MS analysis will be analysed using MassHunter, Mascot and Proteome Scaffold using the Swissprot database. The following parameters will be set during data analysis: MS tolerance; 10 ppm, MS/MS tolerance; 20 ppm, cysteine (carbamidomethylation; fixed modification), TMT labelling will be also selected as fixed modification. Deamidation of asparagine and glutamine will be used as variable modifications, number of missed cleavages; 2, charge states (2^+^, 3^+^, 4^+^) for trypsin, decoy option will be enabled during the analysis. Proteome Scaffold will be used to statistically validate the proteins and peptides identified through Mascot searches as described under the statistical methods section. Protein data will be filtered at 5% FDR and normalized for downstream quantitative analysis. The differentially expressed proteins will be selected after the quantification and selected top proteins (≥1.5-fold) will be further validated through ELISA and Western blotting using the specific primary antibodies using the same follicular fluid samples.

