**Materials and methods:**

An open label single arm trial will be conducted to explore the role of an Ayurveda treatment protocol as a prerequisite for IVF in women with DOR. Forty women diagnosed with DOR satisfying eligibility criteria will be recruited to the study. Out of them, thirty participants will be undergoing Ayurveda treatment prior to their next IVF, and ten participants will be assigned to control group for follicular fluid analysis. Within subject change in serum anti-mullerian hormone and antral follicle count will be the primary outcomes evaluated. The multiomics analysis of follicular fluid will be done in 20 participants recruited to the study (treatment group 10 and control group 10).

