Follicular fluid from 10 control participants and 10 Ayurvedic-treated participants chosen from the 30-participants treatment arm and matched according to age and baseline AMH/AFC will be obtained for the secondary, exploratory multi-omics analysis. All the laboratory experiments will be performed in triplicates (of each biological samples) and statistical analysis will be done using GraphPad Prism software. The statistical analysis of collected proteome data will be performed using Proteome Scaffold software (version 4). Peptide identifications will be accepted if they can be established at greater than 95.0% probability. The Scaffold Local FDR algorithm and peptide prophet algorithm with scaffold delta-mass correction will assign peptide probabilities. Protein identifications will be accepted if they can be established at greater than 99.0% probability and contain at least two peptides representing the protein family. The protein prophet algorithm will assign protein probabilities (34, 35). For metabolomics analysis, after data generation, the heatmaps, principal component analysis, and multivariate statistical analysis will be performed using R (Version 4.5.1) and MetaboAnalyst 6.0. To evaluate the differences between the treatment and control groups in transcriptomics, proteomics, and metabolomics, *t*-tests (for normally distributed data) or Mann–Whitney U tests (for non-normal data) will be used for each gene, protein, or metabolite. To account for multiple comparisons, the Benjamini–Hochberg FDR correction will be used; an FDR of less than 0.05 will be considered significant. As described under each section, specific assays will be used to further validate the most important genes and proteins. No formal sample size calculation was performed for the exploratory multi-omics analysis, as it is hypothesis-generating, and the 10 treatment samples were selected based on matching and feasibility.

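### Twenty follicular-fluid samples need at least two TMT 10-plex sets, but the planned per-protein test has no term for set, so residual set effects could cause false positives or lost power depending on the layout.

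*Protocol article*

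**What the plan says.** The abstract gives the number of samples: "The multiomics analysis of follicular fluid will be done in 20 participants recruited to the study (treatment group 10 and control group 10"). The Sample size and Statistical methods sections repeat the 10 and 10 and say that the groups are matched on age and baseline AMH/AFC.

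Under Proteomics of follicular fluid, quantification is by isobaric labelling: "The solution containing the digested peptides will be subjected to TMT labelling (10 plex) for protein quantification". The same section adds: "Protein data will be filtered at 5% FDR and normalized for downstream quantitative analysis". It names no normalisation method. Selected top proteins with at least a 1.5-fold difference then go to ELISA and Western blot on the same fluid samples.

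Statistical methods fixes the comparison of treatment with control as t-tests "or Mann–Whitney U tests (for non-normal data) will be used for each gene, protein, or metabolite". For multiplicity, "Benjamini–Hochberg FDR correction will be used; an FDR of less than 0.05 will be considered significant". That section also says: "All the laboratory experiments will be performed in triplicates (of each biological samples").

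The article does not say how samples are assigned to labelling sets, and the stated test has no term for set.

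**The concern.** Samples labelled in one set are processed and measured together, and samples in different sets are not. A protein's measured level can therefore shift between sets for reasons unrelated to the women. With two or more sets unavoidable, a two-group test that ignores set can go wrong in two ways.

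- If treated and control samples are unevenly spread over the sets, part of the set shift enters the treatment difference. Benjamini–Hochberg does not help, because it presumes valid p-values for each protein.
- If they are evenly spread, the shift cancels from the difference but stays in the error term, and real differences are missed.

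What is at stake is the list of differential proteins. A stated secondary objective is to identify therapeutic targets by quantitative proteomics, and the list feeds the KEGG analysis. The multi-omics data also go into MOFA and are related to AMH/AFC changes. The layout has to be settled before labelling: if group and set coincide, no later analysis of those data can separate them.

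**Working it through.** **The plan's own figure.** There is none for proteomics. The article says that no formal sample size calculation was made for the multi-omics work. Its one calculated figure, 26 for the within-subject AMH/AFC comparison, reproduces (paired t-test, effect size 0.58, two-sided 0.05: n = 26, power 0.811) but has no bearing here.

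**Number of sets.** Sets = channels needed ÷ usable channels per set, rounded up.

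| Layout | Calculation | Sets |
|---|---|---|
| One channel per woman | 20/10 | 2 |
| Same, one pooled reference channel per set | 20/9 | 3 |
| Triplicates labelled separately | 60/10 | 6 |
| Same, with reference channel | 60/9 | 7 |

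**Size of the effect, two sets.** Inputs from the article: 10 v 10, two-sample t-test. Assumptions: normal log intensities with within-set SD 1; a shift δ between the two sets, *remaining after normalisation*, of 0.5, 1 or 2; unadjusted two-sided 0.05.

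1. *Group and set coincide, no true difference.* The whole shift enters the difference. Noncentrality = δ/√(1/10 + 1/10) = δ√5 = 1.118, 2.236, 4.472 on 18 df. Rejection rate: 18.5%, 56.2%, 98.8%.
2. *7/3 split, no true difference.* Bias = (0.7 − 0.3)δ = 0.4δ, partly offset by a larger pooled SD. Simulated rejection rate: about 6%, 10%, 16%. With set as a block it is about 5% throughout.
3. *Balanced, 5 + 5 per set.* The bias is zero. The expected error variance becomes 1 + 0.25δ² × 10/9 = 1.07, 1.28, 2.11, while the true sampling variance of the difference is unchanged. The planned test is therefore conservative: about 3% false positives at δ = 1 and under 1% at δ = 2.
4. *Balanced, true difference of 1 SD.* Results are in the table.

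| Shift δ | Planned t-test | Set as a block (17 df) |
|---|---|---|
| 0 | 56% | 56% |
| 0.5 | 54% | 56% |
| 1 | 46% | 56% |
| 2 | 24% | 56% |

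**Cross-check with random set effects.** A second simulation drew a random set effect per protein, with SD 0.5, 1 or 2 times the within-set SD, and used a true difference of 1.325 SD (about 80% power with no set effect).

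- Coinciding groups and sets: false-positive rate 0.28, 0.54, 0.75.
- 7/3 split: 0.07, 0.10, 0.14.
- Balanced power, planned t-test: 0.76, 0.65, 0.44, against 0.79–0.80 blocked.
- The Mann–Whitney test behaves the same way (balanced power 0.71, 0.59, 0.38).
- In every layout that is not fully confounded, the blocked model holds its error rate at about 0.05.

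**The case against.** The best defence is that set allocation, channel order and reference channels are laboratory detail, which a journal article leaves to the full protocol or to the standard operating procedures it mentions. That stands as far as the layout goes: its absence from the article is no error. It does not cover the test. The article itself chooses a 10-plex, twenty samples and an unblocked two-group comparison, and these do not fit together well.

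Normalisation may remove much of the problem. A shift common to all proteins would go under even a simple sample-level method, and reference-channel scaling could reduce protein-specific shifts. This stands as a limit on size: only what survives normalisation matters, and the article does not say what the method removes.

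ELISA and Western blot do not depend on the labelling sets and could expose an artefact among the leading proteins. They cover only selected top proteins, recover nothing that was missed, and do not protect the full list used downstream.

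A reader might infer that the plan runs treated women in one set and controls in the other, so that the 56% and 99% describe this trial. The documents do not support that: no section proposes such a layout. Nor can one say flatly that set effects will produce false positives, since under a balanced layout the planned test errs the other way, and at a shift of 0.5 SD its power loss is about 2 percentage points. The rates are also for unadjusted p-values, whereas the plan decides on FDR below 0.05.

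**Conclusion.** The concern holds in a conditional form. At least two labelling sets are certain, and the stated test ignores them. Whether the result is false positives or lost power depends on the unstated layout, and how much depends on the residual set shift, which the documents do not give.

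Over the assumed range of 0.5 to 2 within-set SDs, a moderately uneven split raises a nominal 5% error to between 6% and 16%. A balanced layout costs between about 2 and 32 percentage points of power for a 1 SD difference. The full-confounding figures mark the worst case, not an expectation.

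Priority is low to moderate. The proteomics is secondary and hypothesis-generating, the article disclaims clinical inference between the two groups, and the AMH and AFC analyses are untouched.

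**What to change.** Before labelling:

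- State the number of sets and spread treated and control samples evenly over them: 5 + 5 per set with two sets, or as near balanced as possible if a pooled reference channel makes it three (for example 5 + 4, 4 + 5 and 1 + 1).
- Randomise channel order within each set.
- Name the normalisation method and say whether it uses a reference channel.

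In Statistical methods, for proteomics only, replace the plain two-group test by a linear model on normalised log intensity with treatment group and labelling set as a block. Use one averaged value per woman, so that triplicates are not counted as independent, and then apply the planned Benjamini–Hochberg correction. If triplicates are labelled separately, keep each woman's replicates in one set, or adjust for set before averaging.

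Use a test of within-pair differences only if the matching is one-to-one, which the article does not state. It has 9 df instead of 18, and without within-pair correlation its power at 1 SD is 51%.

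Cost: a labelling order and one degree of freedom per additional set (18 to 17 with two sets). No further participants are needed. A reference channel, if chosen, costs a third set.
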